## Abstract

Introduction: Diffuse sclerosing osteomyelitis (DSO) is a non-bacterial osteomyelitis that occurs infrequently and is characterized by recurrent severe pain, swelling of the mandible, and trismus. To date, no effective treatment has been established. Bisphosphonates have been suggested as an efficacious treatment for DSO; however, no prospective studies have examined the effect of bisphosphonate treatment in adults with DSO. This study aims to evaluate the effect of zoledronate on pain suppression in patients with DSO.

Methods: This is a single-center, exploratory, single-arm, prospective interventional study. The participants will include eight patients with DSO of the mandible. The primary endpoint is the change in pain levels before and after zoledronate administration. The secondary endpoints are assessing the efficacy of the clinical course, imaging changes, and safety monitoring. Patients will be enrolled if they are deemed eligible following screening tests and will receive only one 4.0 mg intravenous dose of zoledronate within seven days of enrollment. Study participants will be followed up at one, four, 12, 24, and 48 weeks post-dose or at discontinuation after zoledronate administration.

Conclusion: This study is the first prospective trial to evaluate the effect of administering a single dose of zoledronate on pain suppression in patients with DSO. We believe this study will lead to the conclusion that zoledronate is an effective treatment for DSO.

## Introduction

Diffuse sclerosing osteomyelitis (DSO) is an infrequent non-bacterial disease of the bone. DSO of the mandible has an estimated prevalence of 1/200,000 [1] and is characterized by recurrent severe pain, swelling of the mandible, and difficulty opening the mouth [1,2]. Radiological examinations reveal diffuse sclerosis and partial osteolysis of the affected mandible [1,2]. DSO is also considered a type of synovitis, acne, pustulosis, hyperostosis, and osteitis (SAPHO) syndrome [3,4], which is a systemic disease proposed by Chamot et al. [5] in 1987; however, the etiology and pathophysiology of DSO remain unclear. Conventional treatment for DSO includes analgesics such as non-steroidal anti-inflammatory drugs (NSAIDs), antimicrobials, hyperbaric oxygen therapy, surgical treatment, and conservative treatment (occlusal sprint, physiotherapy, and myofeedback therapy) [6]. Clinically, symptomatic treatment with analgesics and antimicrobials is common; however, many cases relapse within a short period after showing improvement [7]. Long-term macrolide therapy is considered relatively effective; however, it has disadvantages. It takes time for the patient's condition to improve, complete remission is difficult to achieve, and patients are prone to relapse following drug discontinuation [2].

Intravenous bisphosphonates with bone resorption inhibitory activity are commonly used to inhibit bone resorption in bone metastases from solid tumors and improve hypercalcemia [8]. Bisphosphonates cause serious complications, such as medication-related osteonecrosis of the jaw (MRONJ), and risk factors such as malignancy, duration of antiresorptive therapy, use of corticosteroids, anemia, and diabetes mellitus have been cited [9]. Interestingly, in 2001, intravenous bisphosphonate (pamidronate) was reported to be effective in relieving bone pain in patients with DSO [10]. Since then, the efficacy of oral or intravenous bisphosphonates for treating DSO has been reported in several Japanese studies [11-17], and the development of MRONJ has not been reported. However, the use of oral or intravenous bisphosphonates as therapeutic agents for DSO is not currently approved, and the administration of bisphosphonates in such cases is considered off-label.

A systematic review has suggested that bisphosphonates are the most effective in improving DSO symptoms [6]. If conventional treatments do not improve the condition of patients with DSO, treating them with zoledronate, a bisphosphonate with strong bone resorption inhibitory properties, may be worthwhile. We obtained approval from the clinical ethics committee of Kobe University Hospital for the off-label use of zoledronate to treat DSO in November 2015 (certificate no. 67). Zoledronate was administered to six patients with DSO between November 2015 and February 2018. A single dose of zoledronate reduced mandibular pain in all six patients, and no serious adverse events, including MRONJ, were observed.

DSO causes severe and recurrent pain and a decline in quality of life. A treatment protocol has yet to be established for this disease; therefore, new, highly effective treatments that are fast-acting are required. To date, no prospective studies have examined the effects of bisphosphonate treatment in adults with DSO. Therefore, this study's main objective is to evaluate whether zoledronate has an effect on suppressing pain in patients with DSO who are aware of pain in the mandible.

This trial was retrospectively registered in the Japanese Trial Register (registration number jRCTs051180011).

## Materials and methods

Study design and setting

This exploratory, single-arm, prospective interventional study will only be conducted at Kobe University Hospital. The study will be conducted in a single-arm setting due to difficulties in securing a sufficient sample size owing to disease rarity and lack of standard treatment, as well as its status as a pilot trial for future research.

Patient selection

This study will include patients who meet all the following inclusion criteria. The inclusion criteria include patients aged 20-80 years at the time of consent to participate; diagnosed with DSO based on clinical symptoms, panoramic radiography, mandibular computed tomography (CT), magnetic resonance imaging (MRI), and blood test findings [2]; and who give their free and voluntary written consent to participate in this clinical study.

The exclusion criteria are patients without a diagnosis of DSO based on clinical symptoms, panoramic radiography, mandibular CT, MRI, and blood test findings and with a serum-corrected calcium (Ca) level of ≤8.6 mg/dL determined by a blood test before zoledronate administration. The exclusion criteria also include patients with hepatic dysfunction (serum aspartate aminotransferase (AST) or alanine aminotransferase (ALT) level ≥ 70 IU/L or total bilirubin (T-Bil) ≥ 2.0 mg/dL) and with renal dysfunction (estimated glomerular filtration rate (eGFR) < 30 mL/min). Patients with allergies or other drug sensitivities; a history of QT prolongation, seizures, tetany, numbness, and disorientation associated with hypocalcemia; and MRONJ or a history of MRONJ are also excluded from the study. The exclusion criteria also include patients with the following risk factors for MRONJ: malignancy, angiogenesis inhibitors, corticosteroid therapy, and radiation therapy; with symptoms of otitis externa, ear leakage, or ear pain; and on calcitonin preparations, aminoglycoside antimicrobials, or cinacalcet. Pregnant women and patients who may be pregnant or nursing, patients who participated in another clinical study within four months of participating in the current study, and patients deemed inappropriate for inclusion in the study by the investigators in charge of this clinical research are also excluded from the study.

Interventions

The study participants will be screened after their informed consent has been obtained. Screening tests include a patient background interview, recording of subjective and objective symptoms, vital signs (blood pressure, pulse, and temperature measurements), weight measurements, blood tests, and panoramic radiography and CT imaging. If necessary, analgesics such as NSAIDs and antibacterial agents will be used in combination therapy. Blood tests will be conducted to measure the white blood cell count, leukocyte fraction, red blood cell count, hemoglobin, hematocrit, platelet, AST, ALT, T-Bil, total protein, albumin, blood urea nitrogen (BUN), creatinine (Cr), eGFR, C-reactive protein, sodium, potassium, Ca, and magnesium. Patients will be enrolled if they are deemed eligible after screening tests have been completed and will receive only one 4.0 mg intravenous dose of zoledronate within seven days of enrollment (Figure 1). Zoledronate doses may be reduced according to the degree of renal function: 4.0, 3.5, and 3.0 mg for eGFR > 50, 40-50, and 30-49 mL/min, respectively.

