**Figure 1 FIG1:**
[figure not shown]
Flow chart of the study process to determine and manage the participants. DSO: diffuse sclerosing osteomyelitis

The duration of the clinical study is approximately one year. The patients will be monitored one week before zoledronate administration; on the day of administration; at one, four, 12, 24, and 48 weeks after administration; and at the time of discontinuation. Prohibited concomitant medications include other bone resorption inhibitors (bisphosphonates and denosumab), and the concomitant use of these inhibitors is prohibited throughout this clinical study.

The clinical study will be terminated if continuation of the study is deemed impossible for any of the following reasons: First, the research participants request withdrawal from participation in the clinical study or withdraw their consent. Second, after enrolment, the participants do not satisfy the eligibility requirements. Third, continuing the clinical study due to worsening complications becomes difficult. Fourth, continuing the clinical study due to illness, etc., becomes difficult. Fifth, the entire clinical study is terminated.

Endpoints

The primary endpoint is the amount of change in the mandibular pain assessment index (Visual Analog Scale (VAS): 0-10) from baseline to 48 weeks after treatment (0: no pain; 10: no more pain experienced) [18]. The secondary endpoints are efficacy endpoints including the duration of the pain suppression effect, the extent to which the participant can open their mouth, and the presence or absence of bone with a worm-eaten appearance (indicating resorption) on CT imaging and safety endpoints including the results of blood test results (BUN, Cr, eGFR, and Ca levels) and side effects of zoledronate.

Patient clinical management and follow-up

Study participants will be followed up at one, four, 12, 24, and 48 weeks post-dose or at discontinuation. Self-reported and other symptoms, vital signs, weight measurements, and blood tests will be recorded at each visit. In addition, panoramic radiography or CT imaging will be performed 24 and 48 weeks after administration. Concomitant therapy with analgesics, including NSAIDs and antimicrobials, will be administered, when necessary, for the duration of the clinical study. The different time points are listed in Table 1.

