## Results

The study began in April 2018 and will continue until March 2026. Patients and the public are not directly involved in establishing the research question, study design, outcome measures, recruitment, or conduct of the study. Tables will be prepared for the endpoints; the exact 95% confidence intervals of the binomial distribution will be calculated for each group to compute percentage estimates.

It is hypothesized that the osteolysis of the DSO imaging findings would be associated with symptoms such as pain. It is expected that zoledronate administration, a potent bone resorption inhibitor, will reduce pain by decreasing the osteolysis area. The amount of change in pain before and after the administration of zoledronate is assessed; the closer the VAS value approaches 0 after zoledronate administration, the stronger the pain-suppressing effect of zoledronate on DSO is explained. The change in pain over time is expressed graphically. Moreover, it is expected that zoledronate has an immediate effect on DSO if the pain suppression effect develops early after administration. Concomitantly, if CT images after zoledronate administration show a decrease in the osteolysis area, the decrease in osteolysis is considered to be due to zoledronate administration. In addition, zoledronate is an existing medicine, which explains the safety of zoledronate in patients with DSO if zoledronate administration does not cause serious side effects.

The results of this study will be published in a peer-reviewed international journal. We also plan to present at a scientific meeting to share the results with other researchers in Japan.

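### The renal dose bands overlap: an eGFR of 40 to 49 mL/min is assigned both 3.5 mg and 3.0 mg of zoledronate

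*Protocol article*

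**What the plan says.** The Interventions section (Protocol article, Materials and methods) first gives the standard regimen: an enrolled patient "will receive only one 4.0 mg intravenous dose of zoledronate within seven days of enrollment". It then allows for renal impairment: "Zoledronate doses may be reduced according to the degree of renal function", with the steps "4.0, 3.5, and 3.0 mg for eGFR > 50, 40-50, and 30-49 mL/min, respectively".

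The lower end of the eligible range is set under Patient selection, which excludes patients with "renal dysfunction (estimated glomerular filtration rate (eGFR) < 30 mL/min". Every patient with an eGFR of 30 or more therefore passes the renal criterion.

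The Endpoints section lists among the secondary endpoints "safety endpoints including the results of blood test results (BUN, Cr, eGFR, and Ca levels) and side effects of zoledronate". The Results section says that "The study began in April 2018 and will continue until March 2026".

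**The concern.** A stepped dose table should give each eligible value of renal function exactly one dose. Here two steps share most of their range, so the table gives a patient with an eGFR of, say, 45 both 3.5 mg and 3.0 mg.

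The trial drug is given once, so no later infusion can correct the first. Impaired renal function is the reason for the reduction, and renal blood values are among the safety endpoints. If such a patient's creatinine or eGFR changed after the infusion, a reader would want to know what dose the plan intended and whether it was given. With two doses prescribed for one value, adherence to the dosing rule cannot be judged. The article also calls the study a pilot and foresees multicenter work, so the printed scheme could be copied elsewhere.

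**Working it through.** **Inputs**

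| Item | Value | Place in the protocol article |
|---|---|---|
| 4.0 mg band | eGFR > 50 | Interventions |
| 3.5 mg band | eGFR 40 to 50 | Interventions |
| 3.0 mg band | eGFR 30 to 49 | Interventions |
| Renal exclusion | eGFR < 30 | Patient selection |

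The sentence lists three doses and three bands and pairs them in order, so the mapping itself is not in doubt.

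**Step 1: bands as printed, integer eGFR values**

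- 3.5 mg: {40, …, 50}, 11 values.
- 3.0 mg: {30, …, 49}, 20 values.
- In both: {40, …, 49}, 10 values.
- In at least one: {30, …, 50}, 11 + 20 − 10 = 21 values.
- Share with two doses: 10/21 = 47.6%.
- 3.5 mg only: {50}, 1 value. 3.0 mg only: {30, …, 39}, 10 values.
- No eligible value is left without a dose.

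**Step 2: bands as printed, continuous scale**

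- [40, 50] and [30, 49] intersect in [40, 49], a length of 9.
- The reduced-dose range [30, 50] has a length of 20.
- Share with two doses: 9/20 = 45%.

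**Step 3: are the overlapping values eligible?**

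Yes. The exclusion applies below 30, and 40 to 49 lies above it.

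**Step 4: size of the ambiguity**

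- Difference between the two doses: 3.5 − 3.0 = 0.5 mg.
- Relative to 3.5 mg: 0.5/3.5 = 14.3%. Relative to the standard dose: 0.5/4.0 = 12.5%.

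**Step 5: which limit is likely to be wrong?**

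- If the 3.0 mg band really runs from 30 to 49, the 3.5 mg step keeps one integer value of its own, eGFR 50. That is not a workable middle step. Giving it a useful width would mean moving other limits too, including the cut-off of 50 for the full dose.
- If the 3.0 mg band is 30 to < 40, the overlap falls from 10 integer values to 0 and no value between 30 and 50 is left uncovered. Only one limit changes.

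The second reading is the simplest repair, so a slip in the upper limit of the 3.0 mg band is the likely cause. The article does not state the corrected band, so this remains an inference.

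**The case against.** The overlap itself is hard to dispute; the case on the other side is about its weight.

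- **The article is not the working document.** It condenses a full protocol that is not shown, the trial runs at one hospital, and nothing shows that anyone doses from the article. This stands in part. What is established is a contradiction in the published rule; whether it is in the site's protocol cannot be seen. But condensing explains things left out, not a stated rule that contradicts itself.
- **The wording is permissive.** Doses may be reduced, so clinical judgement is already allowed. That softens the claim that a binding rule fails. It does not explain why the guidance offers two reduced doses for one value. Read literally after the standard 4.0 mg dose, it leaves 4.0, 3.5 and 3.0 mg all open at an eGFR of 45.
- **Figure 1 is not visible and might settle it.** This cannot be excluded. Its caption describes a participant flow chart, and a figure would not correct the printed sentence in any case.
- **The percentages are not patients.** This stands. 48% and 45% describe a range of eGFR values. No eGFR distribution is given, the target is eight participants, and possibly none falls in the overlap.
- **No harm is shown.** This also stands. Both candidate doses are reductions from 4.0 mg, and the article does not show that 0.5 mg alters renal risk. Blood tests are scheduled at every follow-up visit whichever dose is given.
- **The repair is a guess.** The document does not say which limit is wrong, so the sponsor has to confirm it.

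**Conclusion.** The concern holds. As printed, the reduction rule gives two doses to every eGFR from 40 to 49 mL/min, which is nearly half of the reduced-dose range. The contradiction needs no assumption beyond reading the sentence as written; that it is a misprint in the 3.0 mg band is an inference.

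The consequence is confined to clarity of dosing and of safety reporting. It does not touch the sample size, the power or the primary one-sample t-test, and there is no evidence that any patient was misdosed. It should still be fixed, because it is the dosing rule for the only study drug in patients with reduced renal function and the correction costs almost nothing.

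**What to change.** 1. Restate the bands so that each eligible eGFR has one dose, for example 4.0 mg for > 50, 3.5 mg for 40 to 50, and 3.0 mg for 30 to < 40 mL/min. The last limit is assumed here and must be confirmed by the sponsor against its dosing source. Write < 40 rather than 39, since an upper limit of 39 would leave a value such as 39.5 with no dose.
2. State whether the reduction is mandatory. If it is, say that the dose will be reduced.
3. Check that the full protocol used at the site carries the corrected bands.
4. As the study has run since April 2018, look up in the administration record the dose given to any treated patient with an eGFR of 40 to 49, and report it with the renal safety results.

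The cost is a one-line correction and a check of at most eight dose records, the target enrolment. Design, sample size and analysis stay as they are.

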**Figure 1 FIG1:**
[figure not shown]
Flow chart of the study process to determine and manage the participants. DSO: diffuse sclerosing osteomyelitis

The duration of the clinical study is approximately one year. The patients will be monitored one week before zoledronate administration; on the day of administration; at one, four, 12, 24, and 48 weeks after administration; and at the time of discontinuation. Prohibited concomitant medications include other bone resorption inhibitors (bisphosphonates and denosumab), and the concomitant use of these inhibitors is prohibited throughout this clinical study.

The clinical study will be terminated if continuation of the study is deemed impossible for any of the following reasons: First, the research participants request withdrawal from participation in the clinical study or withdraw their consent. Second, after enrolment, the participants do not satisfy the eligibility requirements. Third, continuing the clinical study due to worsening complications becomes difficult. Fourth, continuing the clinical study due to illness, etc., becomes difficult. Fifth, the entire clinical study is terminated.

Endpoints

The primary endpoint is the amount of change in the mandibular pain assessment index (Visual Analog Scale (VAS): 0-10) from baseline to 48 weeks after treatment (0: no pain; 10: no more pain experienced) [18]. The secondary endpoints are efficacy endpoints including the duration of the pain suppression effect, the extent to which the participant can open their mouth, and the presence or absence of bone with a worm-eaten appearance (indicating resorption) on CT imaging and safety endpoints including the results of blood test results (BUN, Cr, eGFR, and Ca levels) and side effects of zoledronate.

Patient clinical management and follow-up

Study participants will be followed up at one, four, 12, 24, and 48 weeks post-dose or at discontinuation. Self-reported and other symptoms, vital signs, weight measurements, and blood tests will be recorded at each visit. In addition, panoramic radiography or CT imaging will be performed 24 and 48 weeks after administration. Concomitant therapy with analgesics, including NSAIDs and antimicrobials, will be administered, when necessary, for the duration of the clinical study. The different time points are listed in Table 1.

**Table 1 TAB1:** Implementation schedule and procedures ○: items to be performed before zoledronate administration; ■: zoledronate administration; ​​​​​​​●: items to be performed following zoledronate administration; ​​​​​​​*: concomitant use of analgesics, including non-steroidal anti-inflammatory drugs and/or antimicrobials

	Screening test	Date of administration	Observation period				
Time point	Before 1 week	0	After 1 week	After 4 weeks	After 12 weeks	After 24 weeks	After 48 weeks
Consent acquisition	○						
Check patient background	○						
Zoledronate administration		■					
Check of subjective and objective symptoms	○	●	●	●	●	●	●
Observation of side effects	○	●	●	●	●	●	●
Vital sign measurement	○	●	●	●	●	●	●
Weight measurement	○	●	●	●	●	●	●
Blood tests conducted	○		●	●	●	●	●
Panoramic radiography conducted	○					●	●
Computed tomography conducted	○					●	●
Concomitant therapy administered^*^	○	●	●	●	●	●	●

Sample size

The target number of participants is eight. Among the reasons for this setting is that the frequency of DSO is extremely low, and only six patients have been administered zoledronate in the past two years in our department. In addition, this clinical study has an exploratory aspect; therefore, the target number of eight cases is considered reasonable. According to the report by Otto et al. [18], a rationale for setting this parameter is that if the changes in the means and standard deviations of the VAS are considered to be six, a one-sample t-test with a significance level of 5% (two-tailed) would yield a power of 80% in eight cases.

Data collection and management

In this clinical study, the clinical research database and clinical research-related documents will be associated with the original data of the research participants using a list of research participant identification numbers. The principal investigator or sub-investigator will prepare a case report form (CRF) for each research participant. The CRF will include the date on which participant consent was obtained, participant identification number, sex, date of birth, age at consent, date of observation, subjective and objective symptoms, vital signs, weight, imaging findings, and blood test results.

Important documents related to the conduct of the research (e.g., materials or records supporting the information used in the study) will be stored in a lockable place for 10 years after the research is discontinued or terminated or 10 years from the date of publication of the research results, such as papers, whichever is later. Thereafter, the documentation will be disposed of in a manner that does not allow the identification of individuals.

Data monitoring

Monitoring will be conducted semi-annually to verify that this clinical research is being conducted safely and in accordance with the protocol and that data is being accurately accumulated. A dedicated staff member will supervise this work.

Statistical analysis

The analysis will be performed after the study drug administration has been completed in all cases and the data have been fixed. For the main analysis, a one-sample t-test will be used to calculate p-values for the change in the pain assessment index (VAS) from one week before to 48 weeks after treatment administration. The significance level is assumed at 5%. For the secondary analysis, the median duration of pain relief, evaluation of the extent to which participants can open their mouths, the percentage of bone resorption measured using CT imaging, and the median value of the duration of the pain reduction effect, as well as their 95% confidence intervals, will be calculated. In addition, changes in the pain assessment index (VAS), BUN, serum Cr, eGFR, and serum Ca levels over time at each time point will be graphed.

We anticipate that missing data are unlikely to arise from the endpoints of the study. However, if significant missing data arise that may have affected the results, they will either be excluded from the study or treated with multiple imputations assuming missing at random.

Ethics approval and consent to participate

Currently, bisphosphonates are used off-label in DSO. Zoledronate is currently being used as an investigational drug for DSO as part of a physician-guided clinical trial in our department. This study was independently reviewed and approved by the Kobe University Clinical Research Ethics Committee (certificate no. C180005) and is being conducted in accordance with the Declaration of Helsinki. Written informed consent will be obtained from all the participants.

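### The primary change starts from one screening VAS taken nominally a week before dosing, so improvement before the infusion is counted in the change credited to zoledronate

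*Protocol article*

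**What the plan says.** All references are to the protocol article.

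- **Endpoints** names a baseline but no visit. Its definition opens: "The primary endpoint is the amount of change in the mandibular pain assessment index (Visual Analog Scale (VAS): 0-10) from baseline to 48 weeks after".
- **Statistical analysis** fixes the visit. The quantity analysed is the "change in the pain assessment index (VAS) from one week before to 48 weeks after treatment administration". The method, given in the same sentence, is that "a one-sample t-test will be used to calculate p-values". In Table 1 the only visit one week before dosing is screening.
- **Interventions** sets the order of events. Enrolment comes after screening: "Patients will be enrolled if they are deemed eligible after screening tests have been completed". Dosing comes later still, since each patient "will receive only one 4.0 mg intravenous dose of zoledronate within seven days of enrollment". One week is therefore nominal. The interval from the screening VAS to the infusion can be longer.
- **The visit schedule below Figure 1** includes a visit on the dosing day: "The patients will be monitored one week before zoledronate administration; on the day of administration". It does not say whether symptoms are assessed before or after the infusion.
- **Table 1** marks the day-0 check of symptoms with the filled circle, which its legend defines as "items to be performed following zoledronate administration". Among the symptom checks, only screening carries the open circle for items done before dosing. The table has no separate VAS row, so the VAS is presumably part of the symptom check.
- **Results** treats a VAS close to zero after dosing as evidence of the drug's strength, and early relief as evidence of an immediate effect.
- **Discussion** concedes that there is no control group and that a placebo effect cannot be excluded. It does not mention regression to the mean or natural fluctuation.

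**The concern.** A one-sample test of mean change against zero credits the drug with everything that happens between the two measurements. Here the first measurement precedes the infusion by a week or more, and pain may move in that time for reasons unrelated to zoledronate. Patients recruited because they hurt tend to hurt less at the next measurement. Analgesics and antimicrobials are permitted from screening onward, and the Discussion says that NSAIDs bring early improvement. The Introduction says of such symptomatic treatment that "many cases relapse within a short period after showing improvement", so short-lived changes in pain are part of the disease as the authors describe it.

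Two conclusions are at stake. The primary p-value would include change that occurred before any drug was given. The planned inference of an immediate effect is also weakened: without a value taken just before the infusion, a fall seen on day 0 or at week 1 cannot be told apart from a fall during the preceding untreated days.

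**Working it through.** **The plan's own figure.** The protocol gives no figure for baseline variability. Its one calculation, 80% power with eight patients for a mean change of 6 and SD of 6, reproduces by the normal approximation: Φ(√8 × 6/6 − 1.96) = 0.807. The exact two-sided t-test gives 68.1%. That is a separate matter and is not used below.

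**Step 1: what the primary change contains.** Let S, D and W be the VAS at screening, just before infusion, and at week 48. Then

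W − S = (D − S) + (W − D).

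The term D − S is entirely pre-drug. It is always inside the primary change, and as Table 1 is marked it cannot be estimated because D is not scheduled.

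**Step 2: assumptions for size.** The documents give only n = 8 and the two-sided 5% one-sample t-test. Everything else is assumed: no drug effect; long-run mean VAS 4; between-patient SD 1.5; within-patient SD and entry level as in three settings, (a) 1.5 and VAS ≥ 5, (b) 2.5 and VAS ≥ 5, (c) 2.5 and VAS ≥ 3; VAS limited to 0–10; week-48 fluctuation independent of the earlier ones. The correlation ρ of a patient's fluctuations between screening and day 0 is varied.

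**Step 3: expected spurious fall.** With s = √(1.5² + SD_w²), a = (cut − 4)/s and λ = φ(a)/(1 − Φ(a)), the fall from the screening baseline, ignoring the scale limits, is (SD_w²/s) × λ:

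- (a) s = 2.121, a = 0.471, λ = 1.12: 1.061 × 1.12 = 1.19
- (b) s = 2.915, a = 0.343, λ = 1.03: 2.144 × 1.03 = 2.21
- (c) s = 2.915, a = −0.343, λ = 0.593: 2.144 × 0.593 = 1.27

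Simulation with the scale limits gives about 1.2, 2.1 and 1.2 points. With a day-0 baseline the fall is about ρ times as large. At ρ = 0.9 that is 0.9 × 1.2 = 1.1 to 0.9 × 2.1 = 1.9, so most of it remains. At ρ = 0 it vanishes.

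**Step 4: false-positive rate of the 5% test (range over the three settings).**

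| ρ, screening to day 0 | Screening baseline | Day-0 baseline |
|---|---|---|
| 0 | 16–45% | about 5% |
| 0.5 | 16–45% | 8–13% |
| 0.8 | 16–45% | 12–27% |
| 0.9 | 16–45% | 14–35% |

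A repeat with 20,000 trials per cell moved these limits by about one percentage point at most. The milder combination (SD 1.5, VAS ≥ 3) gave about 11% from screening and 5 to 9% from day 0. With no selection on pain, both baselines gave about 5%.

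**Step 5: a second parameterisation.** Assume total SD 2.5, correlation of either early value with week 48 of 0.3, and entry at VAS ≥ 5. The screening baseline rejects in about 44%. The day-0 baseline rejects in about 7%, 15% and 31% when the screening-to-day-0 correlation is 0.5, 0.7 and 0.9. The share of the spurious fall that remains is (r₁ − 0.3)/(1 − 0.3): 0.2/0.7 = 29% at 0.5 and 0.6/0.7 = 86% at 0.9.

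**The case against.** A reader might infer that the screening baseline is the reason regression to the mean passes for drug effect, and that a day-0 baseline would bring the error rate back to 5%. The documents do not support that. The root causes are enrolling patients while in pain and having no control, and the Discussion already concedes the second. A day-0 baseline removes only what resolves between screening and infusion. The return to about 5% requires fluctuations with no correlation across the week, and a flare lasting longer than that leaves most of the bias in place.

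Further points against:

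- **Selection on pain is not formalised.** The Introduction describes the target patients as being aware of mandibular pain, but the inclusion criteria set no minimum VAS. The documents do not say that patients are screened at a peak, and the size of the bias depends on this. Some selection is plausible; its degree is unknown.
- **Week-to-week swings are not documented.** Pain is called recurrent, and the relapse statement concerns patients who improved on symptomatic treatment. Neither gives a within-patient SD.
- **Permitted analgesics do not single out this baseline.** They are allowed through week 48, so treatment started after dosing would confound a day-0 baseline too. Only the part started between screening and infusion is specific to this point.
- **The missing pre-dose check rests on a table legend.** The symbols may simply separate the screening column from the rest: even the observation of side effects at screening carries the pre-dose symbol. The day-0 check may in practice precede the infusion.
- **The study began in April 2018.** Patients already dosed cannot supply a new value, and a fallback mixes two baselines among eight patients.

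These points limit the size and the gain. They do not remove the finding. If the day-0 check is in fact pre-dose, the Statistical analysis section still uses the older of two available values, and the correction is then one of wording.

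**Conclusion.** The point holds in limited form. The primary test starts from a single VAS that is nominally a week old at dosing and may be older, and Table 1 as marked schedules no symptom check before the infusion. Pre-dose improvement therefore enters the change that the Results section reads as drug effect, and an early fall cannot be separated from a pre-dose fall. This adds to the bias of an uncontrolled before-after comparison but does not create it.

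The size cannot be fixed from the documents. In every setting examined with selection on pain, the day-0 baseline gave fewer false positives than screening, by a wide margin when pain shifts within a week and by a small one when it persists. Without selection on pain the choice makes no difference to the error rate. The change is worth making because it is specific and cheap, not because it would make a significant p-value causal.

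**What to change.** 1. Record a VAS immediately before the infusion at the existing day-0 visit and give it the pre-dose symbol in Table 1, or state that the existing day-0 check already precedes dosing.
2. Define that value as baseline in the same words under Endpoints and under Statistical analysis.
3. Report the screening-to-day-0 change, which is the trial's only interval without study drug, and keep the change from screening as a sensitivity analysis.
4. For patients already dosed, use a recorded pre-dose day-0 VAS where there is one and the screening value otherwise. Fix this rule before data lock and report how many patients fall under each.
5. Beside the placebo caveat in the Discussion, name regression to the mean and natural fluctuation as limitations, and restrict the causal reading in the Results section accordingly.

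The cost is one VAS at a visit that already takes place, plus wording. The downsides are that only the short-term part of the bias is removed, some patients will lack the new value, and the observed change may be smaller.
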